### ***Maintenance phase***

In the final 12 months, we will stop testing and changing the bundle with PDSA cycles. We expect to achieve maximal system uptake and efficiency by the end of the implementation phase. During maintenance, we will monitor bundle performance with ED dashboards. Change specialists and site champions will use performance measures and site-specific change management strategies to ensure fidelity to the care bundle is high. Champions will share findings in real time with healthcare providers to further promote adherence to the bundle.

## **3. RESEARCH DESIGN**

### **3.1 Design**

To measure the impact of the acute mental healthcare bundle, we will use a quasi-experimental design allows us to study a complex intervention under ‘real world’ conditions so that operational leads have results that are relevant and usable. Data will be collected longitudinally before and after introducing the bundle to services; this approach will allow us to examine, using an interrupted time series approach, how the bundle influenced outcomes relative to the underlying secular trend and competing non-contemporaneous interventions.

### **3.2 Participating centres**

This study involves 2 ‘bundle sites’: Stollery Children’s Hospital, Edmonton; Alberta Children’s Hospital, Calgary.

### **3.3 Patient allocation**

Patients will not be randomized in this study. Care received will be dictated by implementation phase at the two bundle sites (pre-implementation, implementation, maintenance).

### **3.4 Bundle inclusion criteria**

Children and youth eligible to receive the care bundle will be identified by nurses at triage. Eligible children/youth must be aged <18 years and have a mental health complaint in one of the following categories:

- a) Anxiety
- b) Bizarre behaviour
- c) Concern for patient’s welfare

- d) Deliberate self-harm
- e) Depression/suicidal
- f) Homicidal behaviour
- g) Insomnia
- h) Pediatric disruptive behaviour
- i) Situational crisis
- j) Violent behaviour

We will create a pathway for ED healthcare providers to refer to that will describe bundle eligibility criteria in detail. All bundle-eligible children/youth will be triaged, registered, have charts and contact sheets created, and receive care that follows the newly created bundle pathway (see Figure 1). Families opting to stay in the ED to be seen will have triage completed and will be seen as per regular triage priorities and will initially be seen by an ED physician with mental health consultation performed as indicated.

### 3.5 Bundle exclusion criteria

Children and youth not eligible to receive the care bundle will receive acute care following institutional policies. Approximately 20% of all mental health visits (based on site-specific data and the literature) will be by children/youth in an ineligible category:

- a) Brought to the ED by police or peace officers – they bypass triage, go straight to a room, are often restrained, are being held involuntarily, and require urgent physician assessment
- b) Held under Form 10
- c) Features of schizophrenia, schizotypal and delusional disorders (psychosis)
- d) Behavioural syndromes associated with physiologic disturbances (e.g., eating disorders)
- e) Significant intentional self-harm (e.g., laceration, ingestion, hanging)
- f) Previous participation in the study

Patients who do not meet the inclusion criteria and/or who are excluded based on at least 1 exclusion criterion will undergo traditional local care approaches that include physician assessment following triage in keeping with current standards of ED care. In addition, at any point in time, should the patient/family/healthcare team desire deviation from the acute mental healthcare bundle, the family can be switched into the traditional ED care track and based on acuity/urgency, an ED physician will provide a medical evaluation.

### 3.6 Patient recruitment plan

Study recruitment will not occur during the ED visit. Patient partners have told us they do not want to be approached regarding research during the ED visit – therefore will therefore conduct daily reviews of ED medical records at both sites to identify all children and youth eligible for the study. A standardized screening and eligibility confirmation form will be used to guide decision making around study eligibility within REDCap. ED medical records will be reviewed of all children/youth who have a mental health and/or addictions related discharge diagnoses. One of the following CEDIS chief complaints in a child/youth's medical record will indicate potential eligibility:

- a) Anxiety
- b) Bizarre behaviour

- c) Concern for patient's welfare
- d) Deliberate self-harm
- e) Depression/suicidal
- f) Homicidal behaviour
- g) Insomnia
- h) Pediatric disruptive behaviour
- i) Situational crisis
- j) Violent behaviour

Consistent with criteria used to determine bundle ineligibility, a child/youth with the following diagnoses in the medical record will not be contacted to participate in this study:

- a) Brought to the ED by police, peace officers, or ambulance
- b) Held under Form 10
- c) Features of schizophrenia, schizotypal and delusional disorders (psychosis)
- d) Behavioural syndromes associated with physiologic disturbances (e.g., eating disorders)
- e) Significant intentional self-harm (e.g., laceration, ingestion, hanging)
- f) Previous participation in the study

Multiple approaches will be employed to obtain permission for the research team to contact the potential study participant:

- 1) An agent of AHS will approach potentially eligible patients and families in the ED prior to discharge to provide a study information sheet, consent form, and obtain consent to contact.
- 2) For patients who are missed in the ED, we will use the contact information that is collected at ED registration to phone parents/caregivers of eligible children/youth and obtain consent to contact by an agent of AHS. If consent to contact is successfully obtained, appropriate contact information will be collected and documented in this phone call and passed on to the research team.

A research assistant will phone parents/caregivers 24-72 hours after the ED visit to complete recruitment for the study. A standardized script, approved by each institution's ethics board, will be used to obtain written consent. All patients/families who consent to participate in the study will contribute administrative and survey data. Participants can consent verbally to the collection of survey data during the recruitment phone call. Written consent will be required prior to the collection of administrative data from the medical record.

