### 2.1 Improvements to triage in the ED

In the bundle, triage nurses will use the Ask Suicide-Screening Questions. The ASQ tool is validated for pediatric ED patients and is used in many EDs across the US based on its ability to accurately screen for suicide risk among children and youth seeking care. Because healthcare providers differ in how they ask questions, and patient responses are influenced by how questions are posed, a standard approach to risk screening using a robust tool (i.e., the ASQ) identifies patients at risk more accurately. For triage nurses who feel ill-equipped about assess a child/youth's risk, the ASQ is an important tool. In hospitals that use the ASQ, staff report being very comfortable asking the questions. The tool requires minimal training. The goal of the screening is to identify children and youth who require further ED-based assessment to determine the actual level of risk.

The ASQ consists of four yes/no questions, takes 20 seconds to administer, and is available in 13 languages. A child/youth who answers, "Yes" to any question or refuses to answer one, is considered to be 'high risk'. Such children/youth have a threefold high risk for suicide. Children who reply "No" to all questions are considered to be 'low-risk'.

**At Alberta Children's Hospital**, children and youth who screen low-risk on the ASQ will be given a **booked appointment within 24-48 hours at an urgent care clinic** (a partnered mental healthcare clinic located nearby that permits real-time scheduling by ED staff). This approach will ensure families can discuss their needs and concerns—this currently does not occur for low-risk concerns. Families will meet with a nurse or social worker to review the details of their appointment (e.g., date, time, location, and name of clinic staff), and will leave the ED within 30 minutes of arrival.

**At Stollery Children's Hospital**, children and youth who screen low-risk on the ASQ will be able to go to the co-located mental health clinic (located in the hospital) during the clinic's hours. During off-hours, these children and youth will be given a **booked appointment within 24-48 hours at an urgent care clinic** (a partnered mental healthcare clinic located nearby that permits real-time scheduling by ED staff).

ACUTE MENTAL HEALTH BUNDLE **EMERGENCY DEPARTMENT**

[figure not shown]

Figure 1. Care bundle implementation

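### The study's sampling frame does not match the bundle population: ambulance arrivals are excluded from recruitment but not from the bundle, and study screening starts from a discharge diagnosis rather than the triage complaint

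*Protocol*

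**What the plan says.** **Arrival mode.** The bundle exclusions in section 3.5 begin with children "Brought to the ED by police or peace officers". The recruitment exclusions in section 3.6 are introduced with the words "Consistent with criteria used to determine bundle ineligibility", but their first item reads "Brought to the ED by police, peace officers, or ambulance". The other five items, b to f, are the same in both lists.

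**How children are found.** Under section 3.4, triage nurses identify bundle-eligible children by age and one of ten presenting complaints. Section 3.6 starts elsewhere: "ED medical records will be reviewed of all children/youth who have a mental health and/or addictions related discharge diagnoses". It then applies the same ten complaints as CEDIS chief complaints.

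**Earlier participants.** Item f of both lists is "Previous participation in the study". In section 3.5 that item decides who gets bundle care. Section 3.3 says instead: "Care received will be dictated by implementation phase at the two bundle sites".

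**The concern.** The protocol sets out to measure what the bundle does to the children who receive it. For that, the children studied should be the children treated, or a sample of them drawn by a rule that care cannot influence.

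The ambulance item breaks the first condition. A group that may receive the bundle is left out of every survey outcome, and out of those process outcomes that section 3.8 takes from consenting participants.

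The discharge-diagnosis step puts the second condition at risk. The bundle changes who makes the assessment and how. Section 1.2 moves crisis assessment from the ED physician to a mental healthcare provider, and section 2.2 removes medical clearance for high-risk children. Section 2.1 says that, at Alberta Children's Hospital, low-risk families "will leave the ED within 30 minutes of arrival". If any of this alters which children end the visit with a coded mental health diagnosis, the entry filter for the study would shift when the bundle starts. Different children are compared before and after, so such a shift could not be told apart from an effect.

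**Working it through.** **1. The two frames side by side**

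| Step | Bundle (3.4, 3.5) | Study (3.6) |
|---|---|---|
| Entry | Ten complaints, at triage | Mental health/addictions discharge diagnosis, then the same ten complaints |
| Police or peace officers | Excluded | Excluded |
| Ambulance | Not listed | Excluded |
| Previous participation | Excluded | Excluded |

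The frames differ at entry and on ambulance arrival. They do not differ on previous participation.

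**2. Size of the ambulance gap**

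Inputs: 150-200 visits a month (3.10), read as per site because 2,406/12 ≈ 200 (1.1); about 20% ineligible for the bundle (3.5); 75% consent and 75% one-month follow-up (3.10). The ambulance share *a* is not given, so it is assumed.

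- Bundle-eligible visits: 150 × 0.80 = 120, to 200 × 0.80 = 160 per site per month.
- With *a* = 5-20%: 120 × 0.05 = 6, to 160 × 0.20 = 32 treatable but unstudied visits per site per month.
- Patients per interval before any ambulance loss: 120 × 0.75 × 0.75 = 67.5, to 160 × 0.75 × 0.75 = 90. The protocol's figure of at least 50 therefore holds as a lower bound.
- With ambulance loss, 50 is still reached if *a* ≤ 1 − 50/67.5 = 26% (150 visits) or *a* ≤ 1 − 50/90 = 44% (200 visits).

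The gap is one of coverage. It threatens the planned numbers only at high ambulance shares.

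**3. Does either difference act by phase?**

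- *Ambulance:* section 3.6 states the rule once, with no phase condition, so it applies alike before and after.
- *Discharge diagnosis:* it would act by phase only if the bundle changes who receives such a diagnosis. Sections 1.2, 2.1 and 2.2 make that plausible, but nothing in the protocol states or quantifies it. No size can be given.

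**4. Does the bar on earlier participants create a false improvement?**

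Barred children accumulate over 12 + 5 + 12 = 29 months. Assume that the barred share eventually reaches *s* = 10-20%, and that these children score *d* = 3-5 units lower. Barring them then raises the monthly mean by up to *s* × *d*: 0.10 × 3 = 0.3, to 0.20 × 5 = 1.0. This compares the same month with and without the bar. It is not the bias in the planned estimate.

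The segmented model of section 3.11 (baseline level and trend; changes in level and trend for implementation and for maintenance) was fitted to that accumulating shift alone, with no bundle effect. The effect is averaged over maintenance:

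| Pattern | Spurious effect (units) |
|---|---|
| Barred share grows linearly | 0 |
| Share levels off, *s* × *d* × (1 − exp(−*t*/τ)), mid-month *t*, τ = 3-24 months | −0.05 to −0.87 |
| Same, but the bar is reset at the start of maintenance | −0.17 to −1.15 |

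In the levelling-off pattern the raw maintenance-minus-baseline difference is only +0.07 to +0.48. In these scenarios the baseline trend absorbs the shift or over-corrects for it, so any residue runs against the bundle.

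**The case against.** The strongest reply concerns the discharge-diagnosis step. Section 3.4 gives every bundle-eligible child a registration and a chart. The daily record review in section 3.9 counts bundle-eligible children and those booked to a clinic on the triage screen, so children who leave from triage are not invisible. All ten complaints are mental health complaints, so a broad mental health or addictions diagnosis may remove few further children. The 30-minute departure is stated for one site only. All of this stands, and it is why this part is a risk and not a demonstrated bias. It does not explain why a post-care filter is needed when the triage complaint is already recorded and already used.

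On ambulance arrivals, the reply is that a rule constant across phases leaves the before/after contrast intact. That is correct. What remains is the contradiction between the lists and the narrower reach of the results.

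A reader might infer something stronger: that case mix changes with phase, and that barring earlier participants inflates maintenance wellbeing. The documents do not support this. The ambulance rule has no phase condition, and a diagnosis-driven shift is not documented. The bar on earlier participants does accumulate, and the listed covariates do not include prior visits. Under the planned model, however, its effect in the scenarios tried is zero or unfavourable to the bundle.

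**Conclusion.** The point holds as a mismatch of populations. Section 3.6 claims consistency with section 3.5 and does not have it on ambulance arrival; that follows from the text alone. The consequence is limited applicability: 6-32 visits per site per month if 5-20% of eligible visits come by ambulance, a share that is assumed. The difference in entry filters is equally certain from the text. Whether it distorts the comparison between phases is plausible but unproven, and its size cannot be derived. Separately, item f of section 3.5 makes bundle care depend on research history, which does not fit section 3.3.

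No bias in the wellbeing estimate is claimed here. The results for the accumulating bar rest on the assumed shares, deficits and growth patterns shown. They are given only to explain why a false gain of 0.3-1.0 units should not be inferred.

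**What to change.** 1. Reconcile the arrival-mode item in sections 3.5 and 3.6 so that the treated and studied populations match. Which rule applies is for the study team to settle.
2. In all three phases, identify study candidates from the triage CEDIS chief complaint, without requiring a discharge diagnosis. This is the existing second step of section 3.6 made the first.
3. Reconcile item f of section 3.5 with section 3.3, so that it is clear whether earlier research participation affects the care a child receives.

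Allowing one enrolment per child per phase is not recommended as a remedy for the accumulating bar. It would reset the barred share when maintenance starts and create an artificial step under the segmented regression (−0.17 to −1.15 units in the scenarios above, against −0.05 to −0.87 under the present rule).

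The cost is protocol and screening-form wording, and a few more charts to screen.

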### 3.7 Consent and assent

Three methods will be utilized individually and/or in tandem to facilitate the collection of written informed consent and assent:

- (1) **Written Consent:** Participants may sign the hard copy of consent/assent provided by an agent of AHS in the ED. This can be returned to the research team by taking a photo of the signature page and emailing to a secure address. Alternatively the document can be returned by standard mail or email (ie. scanned PDF) to the team.
- (2) **Electronic Consent:** Participants may electronically provide written consent/assent to study participation when contacted by the study team by telephone for recruitment. If this method of consent is chosen by the participant, the research assistant will send a unique URL to a verified

email address or through a text message (utilized from within REDCap) that will link to the REDCap database and allow for the completion of electronic consent.

- (3) **Verbal consent + Written/Electronic Consent:** Participants may provide verbal consent to participating in the survey portion of the study when contacted by the study team by telephone for recruitment. In addition, one of the above two options must be utilized to provide written consent prior to the collection of any health information from the medical record.

All study team contacts with the potential participant will be in accordance with what is outlined in the consent to contact form provided by the agent of AHS. Where applicable, research assistants will ensure copies of the verbal informed consent/assent documents are stored in a locked cabinet and a secure room at each respective study site. The research team will be the only individuals with access to this secure area. At the end of the study, all records will continue to be kept in a secure location for as long a period as dictated by the reviewing research ethics board (minimum of 5 years).

### ***Capacity and mature minors***

As indicated by the University of Calgary Conjoint Health Research Ethics Board, youths that are 14 to 17 years old may be considered mature minors if they have sufficient decision-making capacity. For the purposes of this study, whether the youth will be treated as a mature minor will be determined when the agent of AHS approaches to obtain consent to contact. If the family believes the youth to be the appropriate contact, the research team will treat the youth as a mature minor and the primary contact for the study. In the case of youths 14 years of age or older who attend the emergency department without the presence of a parent or legal guardian and provide their personal contact information when consenting to contact, the study will automatically treat them as mature minors.

When the research team contacts potential participants for recruitment, standard procedures for assessing capacity to consent will be employed. When determining capacity, research staff will assess the following:

- The intelligence of the minor;
- The minor's ability to appreciate the reasonably foreseeable consequences of his or her actions;
- The stage of the minor's physical, emotional, and mental development;
- The degree of responsibility the minor has assumed in his/her life; and
- The inherent risk level of the research protocol

Upon reviewing the study with the minor, the research staff will assess the following:

- Does the minor have the ability to recall study details?
- Does the minor have the ability to identify potential study risks and benefits?
- Does the minor have the ability to formulate and ask informed questions about the study?

### ***Waiver of Consent***

For study participants who enrolled in two time periods, pre-implementation (pre-bundle implementation period) and maintenance (post-bundle implementation period), we will use a waiver of consent to link healthcare visit data outside of the index ED visit. These data will be from Alberta Health and will be used for the economic analysis sub-project (page 15) to understand the impact of the bundle. This sub-project will be submitted as a separate project to the Ethics Board but is noted here for comprehensiveness.

### 3.8 Outcomes and measures

We will target 3 groups of outcome measures—patient-reported, process, and cost—to generate a comprehensive set of data relevant to diverse stakeholder groups.

#### *Patient-reported outcomes and experiences*

The main outcomes of interest for this study include:

- Satisfaction with acute mental health and addictions care
- Consideration of child/youth and parent/caregiver preference for type of follow-up care
- Child/youth wellbeing
- Family wellbeing

**Satisfaction with acute mental healthcare services:** Satisfaction will be measured using the Service Satisfaction Scale (SSS-10), an instrument for measuring global satisfaction with mental health services [Appendices P and Q]. It has several advantages over other measures: brevity, parallel youth and caregiver forms, availability at no cost, and development with data from a large sample of youth and caregivers with rigorous psychometric methodology. It has been routinely employed to evaluate outpatient services in Alberta and was selected by our patient stakeholders over other options provided during stakeholder meetings. The scale consists of 12 items (parent version) or 10 items (youth version) that are relevant to a range of mental health services. Items are scored on a 5-point response scale, with a total possible score of 60 (parent) or 50 (youth) indicating high satisfaction. We will administer the SSS-10 within 24–72 hours of the index ED visit.

**Consideration of child/youth and parent/caregiver preference for type of follow-up care:** CAPA aims to match child/youth family needs and preferences to recommended services. We will measure whether the service met preferences, using a single SSS-10 item about involvement in treatment decisions: “Did you have enough involvement in decisions about your/your child’s treatment?” (Responses: Yes, definitely; Yes, somewhat; No, I wanted to be more involved). The SSS-10 will be administered within 24–72 hours of the index ED visit.

**Child/youth wellbeing:** Wellbeing will be measured with the Stirling Children’s Well-Being Scale (SCWBS) for children aged <13 years and the Warwick-Edinburgh Mental Wellbeing Scale (WEMWBS) for youth aged 13.0–17.99 years. Both scales are required because they are designed for different age groups. The scales assess wellbeing over the previous 2 weeks, are validated across many cultures, and are endorsed for measuring and monitoring wellbeing. We will administer the SCWBS/WEMWBS within 24–72 hours (baseline) of the child/youth’s index ED visit and again at 1 month (primary outcome time-point). The 3-month and 6-month time-points will support assessment of longer-term improvement. These scales measure the same construct in 2 different age groups, so data will be standardized and then combined across age groups to derive a single wellbeing measure.

The SCWBS is a short, robust measure that asks children 12 questions about their emotional and personal wellbeing. The scale has been used to assess change in wellbeing in several studies. The SCWBS covers 3 domains (optimism, cheerfulness and relaxation; satisfying interpersonal relationships; clear thinking and competence) to form a single dimensioned scale of wellbeing. A 5-point response scale is used and scores range from 12–60 with higher scores representing a greater level of wellbeing. The scale was developed and standardized across 18 schools with 1849 children. It has excellent internal consistency (Cronbach’s  $\alpha=0.85$ ) and good test-retest reliability ( $r=0.75$ ).

The WEMWBS scale consists of 14 questions with 5 response categories. Scores range from 14 to 70, higher scores representing a greater level of wellbeing. Focus group discussions with youth suggest that WEMWBS items are clear, user friendly and unambiguous. The scale has been adopted to measure wellbeing among children and youth. It is responsive to changes in different populations across a range of mental health interventions. The scale has excellent internal consistency (Cronbach's  $\alpha = 0.89$ ) and test-retest reliability ( $r = 0.83$ ). It has no ceiling or floor effects and is unsusceptible to bias. It has been validated in a general sample at population and individual level in the UK, and Europe and among ethnic minorities. The WEMWBS is valid and reliable when used with youth receiving secondary care (services for youth with severe mental health conditions that require emergency care or those unresponsive to primary care interventions).

**Family functioning:** Parent/caregiver members of our planning team stressed the importance of understanding our care bundle's impact on family functioning, with the goal of better functioning after a crisis. We will use the Beach Center Family Quality of Life Scale (FQOL) to measure parent report of family functioning. The FQOL is a concise 25-item instrument with questions on parenting, emotional wellbeing, family interaction, physical and material wellbeing, and disability related support. The scale has satisfactory psychometric properties. It uses a 5-point rating scale, with a maximum score of 125 indicating highest quality of life. We will administer the FQOL within 24–72 hours of the initial ED (baseline) visit and again at 1 month.

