## 2.3 Improvements in transitions between healthcare sectors

Currently, there is no standard access to follow-up care and recommendations are often non-specific. The care bundle will introduce Choice from CAPA to urgent care clinics. CAPA is a system transformation model with the goal of improving the flow of mental healthcare delivery through shared decision-making with families. Urgent care clinic resources (i.e., human resources and space) are readily available to support this transformation. In the bundle, Choice will deliver *the right mental healthcare, with the right people, at the right place, at the right time for families*. On the whole, CAPA has been shown to increase family engagement, reduce wait times, result in high satisfaction with services, and reduce ED use. CAPA is grounded in demand/capacity theory and Lean to smooth service flow, creating better patient and staff experiences. Full booking and streamlining of referrals will facilitate 24-48 hour follow-up care in urgent care clinics for children and youth discharged from the ED.

Using CAPA, the follow-up appointment in the urgent clinic will be a *Choice* appointment. It will focus on: a) understanding the main concern(s) and the child/youth/family's strengths, and b) developing joint goal setting and treatment planning. The appointment will conclude with a joint decision on what resources and services best match the family's context, needs, and goals. A *Partnership* appointment (treatment) can be booked as required. This prioritizing of *choice* promotes partnerships between a range of services for families—primarily healthcare, school, social and community-based services. Unique needs and preferences (e.g., newly immigrated, LGBT2Q, financial) are considered, improving the family experience. During this project, as needed, urgent care clinic staff will expand on existing processes for care coordination between services to support interagency connections and seamless transitions. As a result, families will be directly connected to and not required to self-advocate to receive the care they need.

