### ***Process/health system outcomes***

In this project, we will access administrative healthcare data for participant ED visits. ED data will be reviewed for participants who consent/assent to medical record review. We will measure the following outcomes:

- Number of children/youth per month discharged ASQ at triage (low-risk screening outcome) to urgent care follow-up clinic
- Number of children/youth per month who receive psychiatry consultation in the ED after HEADS-ED assessment
- Number of children/youth per month discharged to urgent care clinic after HEADS-ED assessment
- Number of children/youth per month discharged with another recommendation after HEADS-ED assessment, and documentation of the recommendation
- Number of ED visits per month for child/youth mental healthcare that concluded in admission to each children's hospital or transfers to admit at another institution
- Length of ED stay (the interval between time of ED arrival and time of ED departure, either admission or discharge; in minutes) for visits per month to each children's hospital
- Proportion of discharged children/youth who received urgent care clinic follow-up within 48 hours
- Number of child/youth receiving follow-up mental healthcare within 7 days of the ED visit (to be reported by parents/caregivers at 1-month follow-up)
- Number of child/youth receiving follow-up mental healthcare that relates to their index ED visit, within 7 days and 1 month of the index visit
- Appropriate care in the appropriate setting. Research assistants will audit all ED/clinic records monthly at each site and document whether assessments children/youth received are congruent with discharge recommendations
- Type of follow-up care accessed. Parents/caregivers will report types of follow-up care within a month after an ED visit or urgent clinic follow-up appointment

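### The preference outcome is measured only by an item on involvement in decisions, which cannot show that follow-up care matched what the family wanted

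*Protocol*

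**What the plan says.** Protocol section 3.8, under patient-reported outcomes and experiences, lists four main outcomes. One is "Consideration of child/youth and parent/caregiver preference for type of follow-up care". The paragraph defining it begins with the aim of the care model: "CAPA aims to match child/youth family needs and preferences to recommended services". It then fixes the measure: "We will measure whether the service met preferences, using a single SSS-10 item about involvement in treatment decisions".

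The item reads "Did you have enough involvement in decisions about your/your child’s treatment", and the answers are given as "Responses: Yes, definitely; Yes, somewhat; No, I wanted to be more involved". On timing: "The SSS-10 will be administered within 24–72 hours of the index ED visit".

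Two other places bear on the point:
- Section 2.3 puts the matching of services to the family in the Choice appointment at the urgent care clinic: "The appointment will conclude with a joint decision on what resources and services best match the family's context, needs, and goals".
- Section 3.8, under process/health system outcomes, collects the care actually used: "Parents/caregivers will report types of follow-up care within a month after an ED visit or urgent clinic follow-up appointment". That list also contains a monthly audit comparing assessments with discharge recommendations.

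**The concern.** The outcome paragraph promises one construct and assigns an item for another. Whether a preference was met depends on two facts: what type of follow-up the family wanted, and what was recommended or provided. The item asks for neither. It asks whether the respondent had enough say.

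The two can part in both directions. A family may feel fully involved and still leave without the type of care it wanted, for example because that service is not available. Another may feel left out of the decision and yet be referred to exactly what it hoped for.

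At stake is what the trial may conclude on a listed main outcome. The bundle introduces shared decision-making, so involvement is a natural thing for it to change. If a change in this item were reported as preferences being met, the report would claim a better fit between families and services that the data do not contain. The fault lies in the question asked, so no later choice of model or summary can repair it.

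**Working it through.** The plan gives no figure for this outcome, so there is nothing to reproduce. The check sets the promised construct beside the data described.

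**Step 1: what a match needs, and what the protocol describes.**

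| Needed | Where it might be found in the protocol | Present? |
|---|---|---|
| Preferred type of follow-up | SSS-10 item (3.8): asks about amount of involvement | No |
| | Collection table (3.9): SCWBS/WEMWBS, SSS-10, FQOL only | No preference measure listed |
| Type recommended | Process outcomes (3.8): discharge destination and documented recommendation after HEADS-ED | Partly |
| Type received | Process outcomes (3.8): parent/caregiver report of follow-up type | Yes |
| Comparison with preference | Audit (3.8): assessments against discharge recommendations | No, a different comparison |

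Care is recorded; the preference it would be compared with is not.

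**Step 2: what the item can say about the match.** Let *a* be the share answering that they were definitely involved enough. Let *r1* be the share with a preference match among those families, and *r0* the share among all others. The overall match is

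*m* = *a* × *r1* + (1 − *a*) × *r0*.

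The item supplies *a* only. Nothing described in the protocol supplies *r1* or *r0*, so any value of *m* from 0% to 100% is compatible with an observed *a* between 0% and 100%, depending on *r1* and *r0*.

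**Step 3: what a change in the item says about a change in the match.** If *r1* and *r0* stay the same before and after the bundle,

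change in *m* = (change in *a*) × (*r1* − *r0*).

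Suppose, purely as an assumption, that *a* rises from 50% to 70%, a change of 20 points:

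- *r1* = *r0* = 60%: before, 0.50 × 60 + 0.50 × 60 = 60%; after, 0.70 × 60 + 0.30 × 60 = 60%. Change 0 points.
- *r1* − *r0* = 0.5: change 20 × 0.5 = 10 points.
- *r1* = 100%, *r0* = 0%: before 50%, after 70%. Change 20 points.
- *r1* = 0%, *r0* = 100%: before 50%, after 30%. Change −20 points.

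The same 20-point rise in involvement therefore fits any change in match from −20 to +20 points, and a wider range if *r1* or *r0* also move. Only the third case, where involvement and match coincide for every family, lets the item stand in for the match. The protocol gives no evidence for it. These numbers illustrate the logic and predict nothing about this trial.

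**The case against.** The best defence starts from the outcome's label, which speaks of preference being *considered*, not satisfied. Being involved in a decision is a reasonable sign that one's wishes were taken into account. The protocol is also open about the substitution: the defining sentence says what the item is about, and the wording and answers are printed in full. On this view one verb is too strong and the outcome itself is sound.

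Much of this stands. A reader might infer that the outcome is worthless; the documents do not support that, because involvement is a partial proxy for consideration. But the defining paragraph goes beyond its label. It names matching as the aim and says that the meeting of preferences will be measured, and the item cannot carry that part.

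Other stronger readings also fail:

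- *No form in the study records a preference.* The SSS-10 forms are in appendices that are not shown, and neither is the 1-month survey. What can be said is that the protocol text assigns one item to this outcome and describes no question on preferred type of care.
- *The plan will report a false gain.* Section 3.11 sets no contrast or success rule for this item, and none of the five objectives in section 1.2 concerns preference match.
- *Any rise in involvement would be an artefact.* If shared decision-making raises involvement, that is a real effect of the bundle; only calling it a match would be wrong. The size of any rise is also uncertain: Choice appointments are planned at 24–48 hours and the item at 24–72 hours, so some families may answer before the appointment.

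**Conclusion.** Wrong as written, on a secondary point. The protocol says it will measure whether preferences were met, and the only measure it assigns captures perceived involvement. The item can support a statement about involvement and, loosely, about preferences being considered. It cannot support a statement that recommended or received care was what the family wanted.

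The effect on results cannot be sized, because the answers leave the match undetermined. The conclusion rests on the protocol's printed item wording and answers, and on the absence of any described preference question. It would be softened if a form not shown here does ask for the preferred type of care, but the protocol would still need to assign that question to the outcome.

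A reader might infer that the trial's main conclusion is at risk. It is not: wellbeing on the SCWBS/WEMWBS is the primary outcome and the basis of the sample size in section 3.10, and neither depends on this item.

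**What to change.** **Required.** In section 3.8, restate this outcome as perceived involvement in treatment decisions, and remove the statement that the item measures whether preferences were met. Draw no preference-met conclusion from it in any report. This costs a wording change, can be done at any stage, and needs no new data.

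**Only if a match claim is wanted.** Add one question beside the existing 1-month report of follow-up type: was the follow-up that was recommended the type you (your child) wanted? Answers: yes, partly, no. Report separately the families for whom no follow-up was recommended and those who did not receive the care recommended, so that access is not mixed with preference. The question should refer to recommended care, since the protocol's stated aim is to match preferences to recommended services. Use the same wording in every phase.

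**Cost of the added question.**
- Slight extra survey burden.
- The answer is retrospective and may be coloured by later experience of the care.
- It is subject to 1-month attrition: at the 75% follow-up assumed in section 3.10, about 75 of every 100 participants would answer.
- If it is added after the 12-month pre-implementation phase, there is no before/after comparison and the result should be reported descriptively only.
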